##### Physiotherapy intervention

Physiotherapy interventions are detailed in Tables 1, 2 and Additional file 2. These consist of (i) manual hip joint and soft tissue mobilisation and stretching; (ii) hip muscle retraining; (iii) trunk muscle retraining; (iv) functional, proprioceptive and sports- or activity- specific retraining; (v) enhancing physical activity and (vi) education. The treatment will be tailored according to each patient’s clinical presentation (such as strength, pain severity, sporting and functional needs), the presence of co-morbidities (such as back and other lower limb pain or pathology), and progressed based on response to exercise load, thus maximising the training effects. The physiotherapist will supervise exercises during each visit. A home exercise program will be performed independently at home four times per week. An exercise manual will be made accessible to each participant.

**Table 1 Tab1:** **Manual therapy techniques: a semi-standardised approach**

**Manual therapy techniques**				
**Technique**	**Aim**	**Description**	**Dosage**	**Timeframe**
Soft tissue massage and trigger point release of iliopsoas, adductor group, gluteus minimus, gluteus medius, piriformis and tensor fascia latae	Address soft tissue restrictions with the aim of reducing pain and increasing hip joint range of movement	Sustained digital pressure to each trigger point, with the muscle positioned on stretch	30 - 60 seconds digital pressure per trigger point	Session 1 - 8
		Massage longitudinally along the muscle belly	2 - 5 minutes of massage per muscle	
Mobilisation of lumbar spine	To improve lumbar spine mobility and restore normal lumbo-pelvic movement	Unilateral postero-anterior accessory glides, Grade III or IV	3 - 5 sets of 30 - 60 seconds	Session 1 - 8
Correction of sacro-iliac joint asymmetries	To optimise the position of the ilium and therefore the orientation of the acetabulum	Massage to iliopsoas	2 - 5 minutes of massage	Session 1 - 8
		Mobilisation of sacrum		
Manual traction if ligamentum teres is intact or ligated and patient is >3 months post-labral repair	Increase hip flexion and/or IR/ER range of motion	Seatbelt around patient's proximal femur and therapist's hips. Gentle inferior and/or lateral traction force applied. May include patient actively moving hip into flexion as traction is applied	3 sets of 10 seconds. If tolerated, increase by 1 set per treatment session to a maximum of 6 sets in total	Session 1 - 8

Legend: IR = internal rotation; ER = external rotation.

**Table 2 Tab2:** **Home exercise program for hip muscle retraining, trunk muscle retraining, functional and activity specific retraining and stretching: a semi-standardised approach**

**Home exercise program**			
**Exercise**	**Aim**	**Description**	**Timeframe**
Deep hip rotator strengthening	Optimize hip neuromuscular control and improve dynamic stability of hip	See Additional file 2	Session 1 - 4
Hip extensor muscle strengthening	Optimize hip neuromuscular control and improve dynamic stability of hip	See Additional file 2	Session 1 - 6
Hip abductor muscle strengthening	Optimize hip neuromuscular control and improve dynamic stability of hip	See Additional file 2	Session 2 - 8
Functional strengthening	Improve gluteal and lower limb strength. Practice movement patterns required for optimal daily function	See Additional file 2	Session 3 - 8
Balance exercises	Improve proprioception and dynamic stability of hip and pelvis	See Additional file 2	Session 2 - 8
Anterior hip stretch	Assist in regaining full hip extension range of movement	See Additional file 2	Session 2 - 8

Specific aspects of the treatment include:Manual hip joint and soft tissue mobilisation and stretching to provide optimal joint range and facilitate control of movement patterns. Within each treatment session, the therapist will measure range of motion (with an inclinometer), and monitor the immediate effects of treatment modalities.Hip muscle retraining, including exercise to improve hip abduction, extension and external rotator coordination and strength. In order to accommodate a heterogeneous cohort, the hip muscle retraining may be performed statically and/or dynamically in various functional activities (for example, step up and down, squat and/or sit to stand). Resistance will be progressed based on individual responses, and is detailed in Figure 2.Trunk muscle retraining to improve strength, endurance and control of the trunk muscles. The exercise selection and progression will follow similar principles to the hip muscle retraining.Functional, proprioceptive and sports-specific retraining. The exercise selection and progression will follow similar principles to the hip and trunk muscle retraining. For example, a person aiming to return to football may perform single leg activities with direction change and pain-free, graduated return to kicking, whilst maintaining good movement control.

**Figure 2 Fig2:**
[figure not shown]
**Examples of hip exercise progression from non-weight bearing to functional tasks.**

##### Control

In order to control for the psychosocial contact inherent with the physiotherapy treatment, the control treatment will encompass individualised health education sessions covering topics such as exercise, diet, weight loss and appropriate stretching, in a similar fashion to previously published clinical trials looking at physiotherapy management in older people with advanced hip OA [39,40]. The information sheets have been modified to be appropriate for this younger age group. The control sessions will be provided with the same frequency and duration as the physiotherapy sessions.

##### Data management, monitoring and statistical analyses

Treatment efficacy will be evaluated by comparing change on primary outcome measures between groups. Baseline characteristics of participating patients of the two groups will be evaluated for their influence on outcomes and included as covariates in statistical analyses if required. Outcomes of interest will be analysed on an intention-to-treat basis for all participants. SPSS software (Version 21, SPSS Inc, Chicago, IL, USA) will be used for all analyses, and significance will be set at *P* <0.05. Data monitoring will be conducted by an independent investigator (KC), and data will be stored in a locked cabinet and password-secured server. Adverse events will be recorded by the treating physiotherapists who will inform the project coordinator (JK). Trial results will be made available to participants and will be published in a peer-reviewed journal.

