We recently reported that chondrolabral pathology, a marker of early-onset hip OA, is common in people who undergo hip arthroscopy for hip pain, and is associated with worse pain, difficulty participating in physical activity and reduced quality-of-life compared to healthy controls [19]. Moreover, it appears that early onset hip OA has a significant impact on young and middle-aged people being able to participate in physical activities without difficulty, which could ultimately lead to physical inactivity. Inactivity is associated with adverse health outcomes, which include type two diabetes, ischaemic heat disease, stroke, depression and certain cancers [20]. If the progression of hip OA symptoms can be slowed in its early stages, people with hip OA may participate in greater levels of physical activity, limiting the public health burden of this disease [21,22].

A full-scale phase III randomised controlled trial (RCT) is costly, and before undertaking such a study it is important to establish its feasibility [23,24]. In Australia, hip arthroscopy is mostly conducted in the private sector and such patients may be unwilling to participate in an RCT. In addition, no RCT examining the effects of a physiotherapy intervention has been undertaken in this population, and adherence with the intervention is unknown. The treatment algorithm has not been tested within the constraints of a clinical trial and the adverse events are not known. Therefore, before committing to a full-scale RCT, the feasibility of such a study should be established by undertaking a phase II RCT [24].

The primary aim of this study is to establish the feasibility of a phase III RCT investigating a targeted physiotherapy intervention for people with early-onset hip OA. The secondary aims are to determine the size of treatment effects of a physiotherapy intervention, targeted to improve hip joint range and hip-related symptoms in early-onset hip OA following hip arthroscopy, compared to a health-education control.

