### Participants

A total of 20 participants will be recruited through a single orthopedic surgeon ([name]) in Hobart, Australia, with extensive expertise in hip arthroscopy. This number of participants was chosen in order to determine the feasibility of recruitment into a larger scale phase III trial, as we estimate that 20 participants represents 30% of eligible patients from a single surgeon. In addition, 20 participants will allow for observation of sample variability and any possible adverse responses to the intervention. A project investigator (KM) will screen for eligibility based on history and examination.

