### Other measures

#### Potential covariates for statistical analyses

The potential covariates for statistical analyses are body anthropometry: weight, height, body mass index and waist girth.

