## Discussion

This study provides detail of the protocol for a phase II RCT investigating the efficacy of a physiotherapy intervention for early-onset hip OA [24]. This phase II study will identify the willingness of patients to enter a phase III RCT, adherence to the interventions and possible drop-out rates. In addition, this study will provide information regarding the treatment effects sizes of the semi-individualised physiotherapy intervention described, and assist in power calculations which will inform future larger scale RCTs.

The physiotherapy intervention described herein is semi-individualised, wherein a standardised program is tailored to the individual patient’s needs, based on assessment and reassessment undertaken at each physiotherapy session. Impairments in hip range of motion and hip muscle strength have been identified previously in people with chondropathy of the hip [41]. Therefore we have included therapeutic interventions targeted to address these impairments in the physiotherapy intervention.

The control intervention is an alternative physiotherapy intervention, focussing on education and guidance, rather than a ‘wait and see’ control group. This will control for both the attention and advice provided by physiotherapists during individual treatment sessions and may facilitate recruitment, since all patients will receive an active intervention regardless of treatment allocation.

The findings of this study will provide guidance regarding the feasibility of a full-scale phase III RCT, prior to its undertaking [24]. It will also provide pilot data on the efficacy of the physiotherapy intervention described herein.

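### Covariates are to enter after their influence on outcomes has been examined in the same 20 patients, with no criterion, so the treatment effect has no single pre-specified model

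*Protocol article*

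**What the plan says.** Under Data management, monitoring and statistical analyses, the protocol article compares groups on change: "Treatment efficacy will be evaluated by comparing change on primary outcome measures between groups". The primary outcome is feasibility, so I read this as covering the patient outcomes listed as secondary. Baseline characteristics of the two groups then "will be evaluated for their influence on outcomes and included as covariates in statistical analyses if required", and "significance will be set at *P* <0.05".

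Under Potential covariates for statistical analyses, the candidates are listed: "The potential covariates for statistical analyses are body anthropometry: weight, height, body mass index and waist girth". Neither section names the baseline value of the outcome being analysed.

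On size, "A total of 20 participants will be recruited through a single orthopedic surgeon". The number rests on feasibility ("we estimate that 20 participants represents 30% of eligible patients from a single surgeon"), not on power.

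On use, the Background states that "The secondary aims are to determine the size of treatment effects of a physiotherapy intervention", and the Discussion says the study will "assist in power calculations which will inform future larger scale RCTs".

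**The concern.** The article does more than leave the covariate set open. It states a rule, and the rule makes entry depend on how each covariate relates to the outcome in the trial's own data. What counts as required is not defined: there is no threshold, no algorithm, and no statement that the same set applies to every outcome. The anthropometric list narrows the choice, but its members are only potential covariates, and the analysis section speaks more broadly of baseline characteristics.

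Two things are at stake. First, the adjusted effect is not uniquely defined: two analysts following the text could report different estimates from the same 20 patients, each with an interval that ignores the selection step. Second, that estimate has a declared use in sizing a phase III trial. According to Trial status, 17 patients had been recruited and 16 had completed follow-up at submission, so the choice of covariates would be made with most of the data in hand.

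**Working it through.** **No plan figure to reproduce.** The article gives no effect size, SD or power for the efficacy comparison. The only related figure is 20 / 0.30 = 66.7, or about 67 eligible patients.

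**Outcomes affected.** There are 11 secondary outcomes: global change, HOOS-pain, iHOT-33, four other HOOS subscales (quality of life, daily living, sport, symptoms), three strength measures and hip flexion range. Ten have a baseline value. The global change score does not.

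**Inputs.** From the article: 20 patients, two groups, P<0.05 and four candidate covariates. Assumed: 10 per arm, a two-sided test, no true effect, and BMI 26 (SD 4) with weight = BMI × height². Analysis A adds height 172 (SD 9) cm, waist correlated with BMI, baseline to follow-up correlation 0.5, and covariates unrelated to outcome. Analysis B adds height 174 (SD 9) cm, waist–BMI correlation 0.85, and BMI–outcome correlation 0, 0.3 or 0.5.

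**1. Does the written rule inflate type I error?** In A, at least one irrelevant covariate passes a P<0.10 screen in 26% of trials, yet applying that screen mechanically leaves type I error near 5%. In B, mechanical screens at P<0.05 and P<0.20 give 0.050–0.053. So it does not.

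**2. What if the most favourable model is reported?**

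| Choice open to the analyst | Type I error per outcome |
|---|---|
| Best of unadjusted and four single-covariate models (A) | 0.075 |
| Best of all models with up to two covariates (A) | 0.083 |
| Best of all 16 subsets (B) | 0.096–0.117 |
| BMI alone, fixed in advance (B) | 0.051–0.053 |

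The third row comes from a wider choice and different assumptions, so it extends the first two rather than confirming them. I reran A with waist–BMI correlation 0.85: the first two rows came out at 0.072–0.074 and 0.082–0.086, and the mechanical P<0.10 screen at 0.050.

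**3. How far can the estimate move?** In B, across the 16 models on the same patients, the treatment estimate spans a median of 0.24–0.33 SD (90th percentile 0.51–0.64). The unadjusted standard error is about √(2/10) = 0.45 SD (simulated mean 0.44). The model choice can therefore move the estimate by half a standard error or more in a typical trial.

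**4. What does a fixed baseline-adjusted model gain?** Take equal variance σ² at both times, correlation r and n per arm.
- Change score: variance = 2σ²(1 − r) × 2/n.
- Baseline-adjusted: variance = σ²(1 − r²) × 2/n.
- Ratio = (1 − r²) / [2(1 − r)] = (1 + r)/2.

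At r = 0.5 the ratio is 0.75; at 0.3 it is 0.65; at 0.7 it is 0.85. Estimating the slope multiplies the variance by about 1 + 1/(20 − 4) = 17/16 = 1.06, so at r = 0.5 it becomes 0.75 × 1.06 ≈ 0.80. Residual degrees of freedom fall from 18 to 17.

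**The case against.** **Condensed article.** A journal article may leave the exact model to a fuller document, and four candidates are named in advance. That would answer a complaint about silence. It does not answer this one, because the article states an outcome-driven rule, and an analysis plan that followed it would inherit the fault.

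**False positives.** A reader might infer that the rule raises the false-positive rate. The documents do not support that. The screen concerns influence on outcomes, not on the treatment estimate, and such a screen applied mechanically stays near 5%. The higher figures describe selective reporting, which the article neither plans nor rules out. This part of the objection stands.

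**Redundant covariates.** A reader might also infer that the treatment estimate suffers because BMI is a function of weight and height. It does not. Redundancy makes the coefficients of weight, height and BMI unstable, but nobody plans to interpret those, and nothing says that all four would enter together. With 10 per arm, the median variance multiplier for treatment was 0.247 with all four anthropometric covariates and 0.245 with four independent ones.

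**Limited consequence.** Enrolment, recruitment, adherence and drop-out are untouched by covariate adjustment, and the effect sizes are pilot data. This stands too, and it limits the severity.

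**Change score or baseline adjustment.** The choice between them is strictly a separate question. Even so, a fixed model has to contain something, and the baseline value is already collected.

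**Conclusion.** The point holds in a limited form. The article ties covariate entry to outcome relations observed in the same 20 patients, with no criterion, so the treatment effect to be carried into phase III planning is not uniquely defined. The main harm is an estimate that can differ with the model by a median of 0.24–0.33 SD. Type I error stays near 5% under a mechanical screen and reaches about 7.5–8.3% per outcome only if the most favourable of the simpler models is reported.

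These sizes rest on assumed body-size distributions, correlations and equal arms, none of which the article gives. The defect in the wording does not depend on them. Because the primary feasibility outcome is unaffected, severity is minor to moderate.

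**What to change.** Replace the covariate sentence under Data management, monitoring and statistical analyses with a rule fixed before any between-group analysis:

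- For each of the 10 outcomes measured at baseline and 12 weeks, fit one linear model of the 12-week value on treatment group and the baseline value of that outcome. Report the adjusted difference with its 95% confidence interval.
- Compare the six-point global change score between groups without adjustment, since it has no baseline value.
- Drop the screening of baseline characteristics for influence on outcomes.
- Report any anthropometric adjustment only as a labelled sensitivity analysis, using one measure named in advance (such as BMI).

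The cost is wording only, with no new data or procedures. The statistical price is one residual degree of freedom and no adjustment in the main analysis for a chance anthropometric imbalance, which the sensitivity analysis would show.

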### Consent

Written informed consent was obtained from the patients for publication of this manuscript and accompanying images. A copy of the written consent is available for review by the Editor-in-Chief of this journal.

## Discussion

This study provides detail of the protocol for a phase II RCT investigating the efficacy of a physiotherapy intervention for early-onset hip OA [24]. This phase II study will identify the willingness of patients to enter a phase III RCT, adherence to the interventions and possible drop-out rates. In addition, this study will provide information regarding the treatment effects sizes of the semi-individualised physiotherapy intervention described, and assist in power calculations which will inform future larger scale RCTs.

The physiotherapy intervention described herein is semi-individualised, wherein a standardised program is tailored to the individual patient’s needs, based on assessment and reassessment undertaken at each physiotherapy session. Impairments in hip range of motion and hip muscle strength have been identified previously in people with chondropathy of the hip [41]. Therefore we have included therapeutic interventions targeted to address these impairments in the physiotherapy intervention.

The control intervention is an alternative physiotherapy intervention, focussing on education and guidance, rather than a ‘wait and see’ control group. This will control for both the attention and advice provided by physiotherapists during individual treatment sessions and may facilitate recruitment, since all patients will receive an active intervention regardless of treatment allocation.

The findings of this study will provide guidance regarding the feasibility of a full-scale phase III RCT, prior to its undertaking [24]. It will also provide pilot data on the efficacy of the physiotherapy intervention described herein.

## Trial status

This trial is ongoing. At the time of submission of this protocol, 17 patients had been recruited into the study over a four-month recruitment period, and 16 patients had completed the follow-up period. There have been no reported adverse events, drop-outs or patients lost to follow-up to date.

## Abbreviations

HOOS: Hip disability and osteoarthritis outcome score
ICC: Intraclass correlation coefficient
iHOT: International Hip Outcome tool
MCIC: Minimal clinically important change
N: Newton
OA: Osteoarthritis
RCT: Randomised controlled trial
SEM: Standard error of measurement
VAS: Visual analogue scale
WOMAC: Western Ontario MacMaster Universities Osteoarthritis Index
